### Follow-up

All participants will be monitored and evaluated through a structured telephone interview, teleconsultation, and clinical examinations in those without contraindications. This monitoring will be performed by telephone contact with researchers from the coordinating center, which is *Hospital Moinhos de Vento*. The researchers received training for data collection in this modality. The procedures of this stage will be performed in a single telephone exchange located at *Hospital Moinhos de Vento*. Electronic tools (e-mail and WhatsApp) may be used exclusively for scheduling the interviews. Only data on vital status and refusal to follow up will be collected digitally. Medical teleconsultation with the participants will evaluate possible contraindications to undergoing the study exams. After performing the complementary exams, all participants will come to a final teleconsultation that will inform the patients of their exam results and the relevant guidelines for each patient.

Data will be collected using electronic medical records accessible via smartphones, tablets, or computers. The process of digitally collecting and managing data has several benefits over the nonautomated process, such as standardization, reliability, and security of the data collected. The tool used for data collection and management will be the Research Electronic Data Capture (REDCap; https://www.redcapbrasil.com.br/).^(24)^ This data platform will be accessed with a personal and nontransferable username and password, by a member of the team, after due delegation in the study by the principal investigator. Users of the platform (research team) will have specific permissions related to their role and delegation in the study.

### Data security

Several procedures will be employed to ensure the security and quality of the data. All researchers will participate in a training session on good clinical practices and study procedures, including data collection. The researchers will be able to contact the coordinating center of the study to resolve questions or problems that may arise. All processes related to data management complied with the General Data Protection Act (law 13,709 of August 14, 2018). All servers, domain name systems, and means of providing access will be built and maintained in Brazil. This infrastructure will be dedicated to the present study. Therefore, all data will be isolated from any other access, ensuring greater security. In addition, the fact that the servers are headquartered in Brazil will subject the custody of these data to Brazilian law. Digital certificates will also be used for encryption to ensure the security of communications.

The database backup process will be performed automatically every 12 hours. The extraction of data for the statistical software will be done in an automated manner, with data anonymization for checking data consistency, remote monitoring actions, the development of derived variables, and statistical analysis. Data cleaning to identify inconsistencies will be conducted periodically. The researchers will be notified of inconsistencies so that they can correct them. The telephone interviews will be recorded and audited to verify the consistency of the data. The audio files will be stored anonymously on a server with the same security system as the database described. Access to these files will be protected by the research team using a personal, nontransferable username and password. The coordinating center will review monthly detailed reports on triage, inclusion, follow-up, and consistency and completeness of the data. The researchers will immediately take action to resolve any issues. Statistical techniques for fraud identification will be performed throughout the study.

### Calculation of sample size

A sample size of 198 individuals (99 for each group) was calculated to detect a minimum clinically relevant difference of 2mL/minute/mmHg in the mean DLCO between the COVID-19 ARDS patients and healthy controls. Factoring in a 10% rate of losses and refusals, we will need 110 in each group given a desired power of 80%, a significance level of 5%, and a standard deviation of 5mL/minute/mmHg.

### Statistical analysis

The variables will be described as n (%) for qualitative variables, mean ± standard deviation for symmetric quantitative variables, and median (interquartile range) for asymmetric quantitative variables. The distribution of quantitative variables will be assessed by graphical visualization of histograms and the Shapiro–Wilk test. The primary outcome will be compared between the study groups using logistic regression adjusted for sex, age, and comorbidities. The reported measure of effect will be the odds ratio (OR) with its 95% confidence interval (95%CI). The secondary outcomes with qualitative distributions will be evaluated in the same way as the primary outcome. The quantitative distribution of secondary outcomes will be evaluated by means of multiple linear regression adjusted for sex, age, and comorbidities. The reported measure of effect will be the difference in means with their 95%CIs. P values < 0.05 will be considered statistically significant. Secondary outcomes will not be adjusted for multiple variables. Thus, the findings for the secondary outcomes will be interpreted as exploratory. The analyses will be performed with R software packages to be detailed at the time of analysis.^(25)^

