## METHODS

This is a prospective, multicenter case–control study of patients who survived hospitalization for COVID-19 and were diagnosed with ARDS and controls without persistent symptoms of COVID-19 and hospitalization due to clinical disease in the last 12 months. The study design is summarized in figure 1. The study protocol is registered at Clinicaltrials.gov (NCT05225194). This study was approved by the National Research Ethics Committee (Conep) (CAAE: 54943222.7.1001.5330) and adheres to resolution 466/12 of the National Health Council (CNS) of Brazil. Free and informed consent will be obtained from all participants.

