### Outcomes

The primary outcome of the study is the pulmonary diffusing capacity for carbon monoxide (DLCO) measured after 12 months. The following were considered secondary outcomes: physical-functional capacity measured by the modified Barthel index after 12 months;^(18)^ instrumental activities of daily living measured by the Lawton and Brody scale of instrumental activities of daily living from 12 months onward;^(19)^ muscle function and strength assessed by Strength, Assistance with Walking, Rising from a Chair, Climbing Stairs, and Falls (SARC-F) at 12 months of age;^(20)^ dyspnea measured by the modified *Medical Research Council* (MRC) dyspnea scale from 12 months of age;^(21)^ health-related quality of life assessed using the EuroQol 5 Dimensions 3 Levels questionnaire (EQ-5D-3L) from 12 months onward;^(22.23)^ ergospirometric variables from 12 months onward: direct oxygen consumption, maximum oxygen consumption (VO_2_ peak), minute volume/CO_2_ production ratio (VE/VCO_2_ slope) and oxygen uptake efficiency (OUES - Oxygen Uptake Efficiency Slope); spirometric variables from 12 months onward: vital capacity (VC), forced expiratory volume in one second (FEV1) and FEV1/VC; and radiological patterns of pulmonary fibrosis assessed by high-resolution tomography of the chest from 12 months onward; radiological patterns related to the sequelae of acute myocarditis assessed by cardiac magnetic resonance imaging with T1- and T2-weighted parametric maps and by means of the delayed enhancement technique from 12 months onward; radiological patterns of sarcopenia assessed by high-resolution tomography of the chest from 12 months onward; changes in renal function or structure assessed by magnetic resonance imaging and laboratory tests; and major cardiovascular events (non-fatal infarction, non-fatal stroke, acute heart failure) and thromboembolic events (deep venous thrombosis, pulmonary embolism) after hospital discharge. The data collection protocol for the exams collected is described in the Supplementary Material.

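### The study is sized on a difference in mean DLCO, but the primary analysis is a logistic regression reporting an odds ratio, which does not estimate that difference

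*Protocol article*

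**What the plan says.** Three sections of the protocol article bear on the point.

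- **Outcomes:** "The primary outcome of the study is the pulmonary diffusing capacity for carbon monoxide (DLCO) measured after 12 months". No threshold, category or event based on DLCO is given here or elsewhere in the article.
- **Calculation of sample size:** 99 per group were calculated "to detect a minimum clinically relevant difference of 2mL/minute/mmHg in the mean DLCO between the COVID-19 ARDS patients and healthy controls", with SD 5 mL/min/mmHg, 80% power and a 5% significance level. Allowing for 10% losses and refusals gives 110 per group.
- **Statistical analysis:** "The primary outcome will be compared between the study groups using logistic regression adjusted for sex, age, and comorbidities". The effect measure follows: "The reported measure of effect will be the odds ratio (OR) with its 95% confidence interval (95%CI". Qualitative secondary outcomes are to be handled as the primary outcome is. For the rest, "The quantitative distribution of secondary outcomes will be evaluated by means of multiple linear regression adjusted for sex, age, and comorbidities" and "The reported measure of effect will be the difference in means with their 95%CIs".

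**The concern.** The Statistical analysis section holds two rules: a logistic model with an odds ratio, and a linear model with a difference in means. DLCO is quantitative and the sample size is for its mean, so it belongs under the second rule. The text puts it under the first, together with the qualitative secondary outcomes.

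The study's one confirmatory result depends on that sentence. An analyst following it must either turn DLCO into a binary variable or make group membership the response. The article does not say which. The two choices answer different questions and have different power, and neither yields a difference in mL/min/mmHg that can be set against the 2 mL/min/mmHg called clinically relevant. The slip also spreads, because the method for qualitative secondary outcomes is defined only by reference to the primary outcome.

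**Working it through.** **Inputs from the Calculation of sample size section:** difference 2, SD 5 (standardised difference 2/5 = 0.4), power 80%, alpha 5%, 99 evaluable per group, 10% losses. Sidedness is not stated. Two-sided alpha reproduces the figure, whereas one-sided alpha would give 78 per group.

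**1. Reproduce the plan's figure as a comparison of means.**

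n per group = 2 × (1.960 + 0.8416)² / 0.4² = 98.1, rounded up to 99.

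At 99 per group, power is 80.4% by the normal approximation and 79.97% by the t-test. With losses, 99 / 0.90 = 110 per group, 220 in total. The stated numbers are correct, and they are for a mean difference.

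**2. Reading A: DLCO is dichotomised and used as the response.** The article gives no cut-off, so those below are assumptions. DLCO is taken as normal with SD 5 in both groups and a mean lower by 2 in patients. With p0 the proportion of controls below the cut:

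- p1 = Φ(Φ⁻¹(p0) + 0.4), and p̄ = (p0 + p1)/2
- power = Φ{[(p1 − p0) − 1.96 √(2p̄(1 − p̄)/99)] / √([p0(1 − p0) + p1(1 − p1)]/99)}

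For the midpoint cut, p0 = 0.421 and p1 = 0.579, so power = Φ[(0.1585 − 1.96 × 0.0711)/0.0702] = Φ(0.274) = 0.61.

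| Assumed cut | Controls below | Patients below | Odds ratio | Power at 99 per group | Evaluable per group for 80% |
|---|---|---|---|---|---|
| Midway between the means | 42.1% | 57.9% | 1.90 | 61% | 155 |
| 20% of controls below | 20.0% | 32.9% | 1.96 | 54% | 182 |
| 1 SD below control mean | 15.9% | 27.4% | 2.00 | 51% | 199 |
| 5% of controls below | 5.0% | 10.7% | 2.27 | 32% | 353 |

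The last column solves the same formula for n: [1.96 √(2p̄(1 − p̄)) + 0.8416 √(p0(1 − p0) + p1(1 − p1))]² / (p1 − p0)².

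A simulation of the unadjusted logistic model at the midpoint cut (3,000 runs, 99 per group) gave 63%, in line with the formula.

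**3. Reading B: group is the response and continuous DLCO the predictor.** In the same simulation this model rejected in 80.0% of runs, against 80.5% for the linear model. Power is kept. The estimate, however, is an odds ratio of being an ARDS case per mL/min/mmHg of DLCO. With normal data and a common SD, its expected value is exp(−2/25) = 0.92. It is not a mean difference.

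**4. Linear model.** This is the comparison that step 1 reproduces, so 99 (110) per group needs no change. Neither the plan's calculation nor these checks allow for the covariates.

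**The case against.** The best defence starts from the design label. The article calls this a case–control study, and in that design regressing case status on a measured variable and reporting an odds ratio is customary. The sentence on the primary outcome does not name the response variable. On that reading the model needs no cut-off and keeps about 80% power. A DLCO threshold could also sit in a full protocol or SAP that is not shown.

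Much of this stands, and it limits the point. A reader might infer that the analysis cannot be run at all, or that any way of running it loses the stated power. The documents do not support either, because Reading B runs and keeps the power. A reader might also infer that a cut-off would be chosen after seeing the data. All that can be said is that no cut-off appears in the article and that the sample size is not built on one. Nor does the article show that the case–control label led to the odds ratio, and the repair does not require the design to be renamed.

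The defence does not remove the mismatch. Under either reading the reported quantity is an odds ratio, while the sample size is for a "minimum clinically relevant difference of 2mL/minute/mmHg in the mean DLCO". Applying the primary outcome's method to qualitative secondary outcomes also points to a categorical primary outcome, which the Outcomes section does not define. Condensation into an article does not explain this, since the model and the effect measure are both stated outright.

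**Conclusion.** Wrong as written. The stated primary analysis does not estimate the quantity for which the study is sized, and this holds whichever way the logistic model is set up.

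The cost depends on the reading. With a dichotomised DLCO, power at 99 per group is about 61%, 54% or 32% at the midpoint, 20%-of-controls and 5%-of-controls cuts. These figures illustrate assumed cut-offs, normality and a common SD; they are not properties of the plan. With group regressed on continuous DLCO there is no material loss of power, only an effect measure on the wrong scale and in the wrong direction. It would be too strong to call the study underpowered: the sample size is correct for the comparison of means it describes.

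**What to change.** In the Statistical analysis section, replace the primary outcome rule and its effect measure with: DLCO (mL/min/mmHg) will be compared between the groups by multiple linear regression adjusted for sex, age and comorbidities, and the adjusted difference in means will be reported with its 95% CI.

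Then state separately that qualitative secondary outcomes will be analysed by logistic regression with the same covariates, reporting odds ratios with 95% CIs, so that their method no longer depends on the primary outcome's.

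If a DLCO category is what the investigators want, it would have to be defined in the Outcomes section and the study re-sized for it; the table above indicates 155 to 353 evaluable per group under the assumed cut-offs. The linear model is the cheaper course and agrees with the existing calculation. It costs a change of wording in the protocol, and in the SAP if that repeats the rule, with no new data and no change to the 99 (110) per group.

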**Methods::**

This will be a multicenter case–control study of 220 participants. Eligible are patients who are hospitalized for acute respiratory distress syndrome due to COVID-19. In the control group, individuals with no history of hospitalization in the last 12 months or long-term symptoms of COVID-19 will be selected. All individuals will be subjected to pulmonary spirometry with a carbon monoxide diffusion test, chest tomography, cardiac and renal magnetic resonance imaging with gadolinium, ergospirometry, serum and urinary creatinine, total protein, and urinary microalbuminuria, in addition to quality-of-life questionnaires. Patients will be evaluated 12 months after hospital discharge, and controls will be evaluated within 90 days of inclusion in the study. For all the statistical analyses, p < 0.05 is the threshold for significance.

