### Patient selection

#### Patients with acute respiratory distress syndrome

Patients will be considered eligible if they are ≥ 18 years of age, have a positive reverse transcription polymerase chain reaction (RT-PCR) test or a positive antigen test for SARS-CoV-2 infection collected via nasopharyngeal swab during hospitalization or within 14 days beforehand, and are diagnosed with ARDS due to COVID-19 during hospitalization, and hospital discharge from the index hospitalization. The diagnosis of ARDS was defined according to the Berlin criteria:^(17)^ respiratory failure not fully explained by heart failure or fluid overload; onset within one week of the known lesion or new symptoms that worsened; bilateral opacities not fully explained by effusions, lobar collapse, lung collapse, or nodules; hypoxemia defined as the relationship between partial pressure of oxygen and fraction of inspired oxygen (PaO_2_/FiO_2_) ≤ 300mmHg, with positive end-expiratory pressure or continuous positive airway pressure ≥ 5cmH_2_O. The exclusion criteria are severe underlying disease with a life expectancy less than 3 months, unwillingness to undergo the tests to be performed, absence of a family member if the patient has communication difficulties (aphasia, cognitive impairment, nonnative speakers of Portuguese), and nonconsent to participate in the study.

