#### Controls

Individuals ≥ 18 years of age who are family members or social interactors of participants who have survived ARDS due to COVID-19 will be considered controls. Individuals who are unwilling to undergo the proposed tests, have a history of persistent symptoms after SARS-CoV-2 infection, have a history of nonelective hospitalization due to clinical disease in the last 12 months, have a severe underlying disease with a life expectancy of less than 3 months, or do not consent to participate in the study will be ineligible. The following symptoms are considered persistent symptoms of COVID-19: cough, fatigue, muscle pain, dyspnea, anosmia, ageusia, and memory or concentration deficit, as previously evaluated by a physician and attributed to COVID-19.

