### Procedures

All participants will undergo teleconsultation by telephone to evaluate possible contraindications for the following complementary exams: serum creatinine and urea, creatinine and total protein in urine, microalbuminuria and qualitative urinalysis; spirometry with pulmonary diffusion for carbon monoxide (CO_2_) without a bronchodilator test; treadmill ergospirometry with a ramp protocol; high-resolution tomography of the chest (noncontrast); and cardiac and renal magnetic resonance imaging with gadolinium contrast. Patients with contraindications to one or more exams who are eligible will remain in the study. Teleconsultation and exams will be performed between 12 and 36 months after discharge from the index hospitalization for ARDS or, for controls, at the time of inclusion (with a restricted window of up to 90 days due to the risk of controls developing COVID-19 or other clinical complications after the initial visit). Figure 2 is the flow chart of the participants in the study.

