Acute kidney injury is a common complication in the acute phase of COVID-19 and is associated with worse outcomes and progression to chronic kidney disease, especially in those with greater severity at presentation.^(12)^ The factors that may be associated with kidney injury caused by COVID-19 include viral agent-mediated endothelial damage, complement activation, local inflammation, and glomerulopathy,^(11)^ as well as other factors such as hemodynamic status in acute infection, nephrotoxic medication, and thrombotic events, among other indirect agents.^(31)^ Long-term kidney damage may be related not only to the direct maintenance of the offending agent but also indirectly to the exacerbation of cardiovascular diseases that lead to greater kidney damage.^(11)^ We hope to estimate the long-term prevalence of renal damage associated with COVID-19 in the Brazilian population by measuring kidney function and examining its structure.

This study will have several strengths. It is a multicenter study that will prospectively evaluate long-term sequelae. Many of the previous studies that investigated long-term COVID-19 and its sequelae included patients shortly after acute infection.^(13.28)^ Due to the few cases and the severity of COVID-19, the patients included may have come from the earlier stages of the pandemic. In addition, the retrospective collection of data regarding index hospitalization may limit our study.

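### The design is labelled case–control although groups are formed by exposure, and qualitative outcomes get only an odds ratio as between-group measure although the stated interest is prevalence

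*Protocol article*

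**What the plan says.** **Label.** The abstract states: "This will be a multicenter case–control study of 220 participants". The Methods section repeats it: "This is a prospective, multicenter case–control study of patients who survived hospitalization for COVID-19".

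**Selection.** The patient group is made up of adults who "are diagnosed with ARDS due to COVID-19 during hospitalization, and hospital discharge from the index hospitalization". The Controls section defines the comparison group: "Individuals ≥ 18 years of age who are family members or social interactors of participants who have survived ARDS due to COVID-19 will be considered" (the sentence ends by naming them as the control group). People with persistent symptoms after infection, or with a non-elective hospital stay for clinical disease in the past 12 months, are excluded from it.

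**Timing.** The Procedures section says: "Teleconsultation and exams will be performed between 12 and 36 months after discharge from the index hospitalization for ARDS". Controls are examined at inclusion, within a 90-day window.

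**Analysis.** In the Statistical analysis section, the primary outcome is compared by logistic regression adjusted for age, sex and comorbidities, and "The reported measure of effect will be the odds ratio (OR) with its 95% confidence interval (95%CI"). Qualitative secondary outcomes are handled identically. Quantitative secondary outcomes get an adjusted difference in means, and qualitative variables are described by counts and percentages.

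**Aim.** The Discussion says of the kidney: "We hope to estimate the long-term prevalence of renal damage associated with COVID-19 in the Brazilian population". It states a similar prevalence aim for long-term cardiac sequelae.

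**The concern.** In a case–control study, participants are sampled on the outcome. The sample's outcome frequency is then fixed by design, prevalence cannot be read from it, and the odds ratio is the natural contrast. None of that applies here. Nobody is sampled on fibrosis, myocardial pattern, sarcopenia on CT or renal change. The label therefore tells readers that the study cannot do something its Discussion says it will do.

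The choice of effect measure fits the label better than the aim. For qualitative outcomes the plan names no adjusted difference or ratio of prevalences. A reader interested in the burden of sequelae will be tempted to read the odds ratio as how many times more frequent a finding is in survivors. For common findings that reading exaggerates the contrast. The odds ratio also does not give the absolute difference, which matters most for the planning of health services that the Discussion mentions.

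**Working it through.** **1. Design, by setting the sections side by side.**
- Patients enter because of an exposure: ARDS due to COVID-19, survived to discharge (Patients with acute respiratory distress syndrome).
- Controls enter as relatives or social contacts without that exposure (Controls).
- Outcomes are examined afterwards, once, in both groups (Procedures; Outcomes).

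Selection is by exposure and measurement of outcome follows. This is an exposed/unexposed comparison, not sampling on the outcome.

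**2. Effect measures named in Statistical analysis.**
- DLCO (primary): odds ratio.
- Qualitative secondary outcomes: odds ratio.
- Quantitative secondary outcomes: difference in means.
- Description of qualitative variables: n (%).

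For qualitative outcomes the odds ratio is thus the only between-group measure. Percentages by group allow a crude ratio or difference to be worked out, but not an adjusted one.

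**3. Odds ratio against prevalence ratio.** Let p0 be the prevalence in controls and p1 the prevalence in patients.
- Prevalence ratio: PR = p1/p0
- Odds ratio: OR = [p1/(1 − p1)] / [p0/(1 − p0)] = PR × (1 − p0)/(1 − p1)

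The article gives no prevalences for its outcomes, so every p0 and PR below is an assumption.

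| p0 | p1 if PR = 2 | OR | Difference | p1 if PR = 1.5 | OR | Difference |
|---|---|---|---|---|---|---|
| 5% | 10% | 2.11 | 5 points | 7.5% | 1.54 | 2.5 points |
| 10% | 20% | 2.25 | 10 points | 15% | 1.59 | 5 points |
| 20% | 40% | 2.67 | 20 points | 30% | 1.71 | 10 points |
| 30% | 60% | 3.50 | 30 points | 45% | 1.91 | 15 points |
| 40% | 80% | 6.00 | 40 points | 60% | 2.25 | 20 points |

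Example, p0 = 30% and PR = 2: (0.60/0.40)/(0.30/0.70) = 1.50/0.4286 = 3.50. This is 3.50/2 = 1.75 times the true ratio. At p0 = 5% the factor is 2.11/2 = 1.06.

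An odds ratio of 2.25 appears twice in the table: for 10% against 20% (ratio 2, difference 10 points) and for 40% against 60% (ratio 1.5, difference 20 points). The odds ratio alone does not distinguish the two.

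**4. Planned size.** The Calculation of sample size section uses a difference in mean DLCO of 2, a standard deviation of 5, 80% power and a 5% level. Sidedness is not stated; two-sided reproduces the figure, while one-sided would give 78 per group.
- n = 2 × (1.960 + 0.842)² × 5²/2² = 98.1, rounded up to 99 per group
- With 10% losses: 99/0.90 = 110 per group, 220 in total

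The stated figures are reproduced. They rest on a mean difference, so adding effect measures for qualitative outcomes leaves them unchanged.

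**The case against.** Several objections have force.

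- **Other measures are planned.** A reader might infer that the study reports nothing but odds ratios. It does not: quantitative secondary outcomes get mean differences and qualitative ones get n (%). The point is limited to the between-group contrast for qualitative outcomes. Whether the percentages also carry confidence intervals is detail that an article may leave to the full plan.
- **The odds ratio is valid.** It is a legitimate measure in a cohort and misleads only when read as a prevalence ratio. At control prevalences of 5% to 10% and a true ratio of 2 it is 2.11 to 2.25, a small gap.
- **Nothing shows that outcomes will be common.** A reader might take the Discussion's mention of frequent lung abnormalities as a forecast. It is another cohort's result at 3 months, and this study examines patients from 12 months on. The size of the overstatement is therefore unknown.
- **The quoted sentence first concerns DLCO.** DLCO is continuous and has no prevalence. Whether logistic regression suits it is a separate matter and no part of this point. The odds ratio reaches the qualitative outcomes through the later sentence that applies the same method to them.
- **Prevalence contrasts do not suit every outcome.** Cardiovascular and thromboembolic events accrue after discharge over a variable 12 to 36 months. Controls with persistent symptoms, dyspnea among them, are excluded, which distorts symptom comparisons. Selection of this kind affects an odds ratio as well, so it narrows the scope of the change without favouring the odds ratio.
- **These outcomes are exploratory, and selection is openly described.** Both are true, and they limit the weight of the point.

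What survives is that the label contradicts the sampling, and that the only contrast named for qualitative outcomes does not match the prevalence aim.

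**Conclusion.** The point holds within limits. The case–control label is wrong for the sampling described, and this follows from the article's own sections without any assumption. For qualitative secondary outcomes, the sole between-group measure is an adjusted odds ratio, although prevalence is a stated interest and adjusted prevalence contrasts can be estimated from the same data.

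The size is conditional. If outcomes are rare in both groups, the odds ratio and the prevalence ratio nearly agree. From control prevalences of about 20% upward they part clearly: for a true ratio of 2, the odds ratio is 2.67 at 20% and 3.50 at 30%. All these prevalences are assumed.

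A reader might go further and conclude that the planned odds ratios are biased, or that the study's effects will be overstated. The documents do not support that, because the overstatement arises only from misreading the odds ratio and only for common outcomes. Conversely, a cohort label would not by itself make the group percentages representative of all Brazilian survivors. They describe the people recruited, from centres in and around Porto Alegre.

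This is a worthwhile correction to the description and reporting. It does not undermine the study.

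**What to change.** - **Design label.** In the abstract and Methods, replace case–control with an exposed/unexposed cohort comparison with a single assessment.
- **Effect measures.** For binary outcomes assessed at the examination (for example, CT patterns of fibrosis or sarcopenia, cardiac MRI patterns, and renal findings where analysed as present or absent), add the adjusted prevalence difference and prevalence ratio with 95% confidence intervals. Fit the planned logistic model, predict each participant's probability with group set to patient and then to control, average each set of predictions, and take their difference and ratio. Poisson regression with robust errors is an alternative for the ratio. Keep the odds ratio alongside.
- **Scope.** State that this does not apply to DLCO, quantitative secondary outcomes or post-discharge events, and that symptom outcomes need a caution because controls with persistent symptoms are excluded.

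The cost is a change of wording and a few lines of R on the same data. No participants or examinations are added, and the planned 220 stands. The one small drawback is that, when a finding is more frequent in patients, the prevalence ratio will look less striking than the odds ratio.
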